### Data management and monitoring

The CRC will check the completeness of the study documents at the polyclinic before transferring them to Duke-NUS. Such transfers will be acknowledged and documented in a log file maintained by the study team. To ensure confidentiality, only de-identified research data will be passed to Duke-NUS. Study team members at Duke-NUS will digitise the responses from the paper-based questionnaires and checklists into a data entry Excel file. Data will be double-entered for accuracy by two separate members of the Duke-NUS team. To further minimise errors, the data entry sheets have been designed to only accept values that are within the correct range.

Once the first 80 participants have successfully completed the month-6 assessments, the following outcomes will be assessed by a trained statistician: HbA1c levels and adherence across physical activity, medication and blood glucose testing rates and levels. These will be repeated when 160 participants complete the month-6 assessment. Further, attrition and missing data patterns will be analysed. The purpose of these interim analyses is to detect potential issues that might have arisen during the data collection process before the end of the trial and to report preliminary results to SingHealth Centralised Institutional Review Board (CIRB) on an annual basis. No stopping rules have been defined for this trial.

The CRC will ask participants about potential adverse events. If a patient has been hospitalised during the intervention, the CRC will record the details. Reporting of adverse events involves notifying the SingHealth CIRB and submitting the Serious Adverse Events (SAE) Reporting Form within the stipulated timeframe. The notifying and reporting requirements depend on the severity, nature and causality of the event and there are specific procedures that must be followed [33].

No data monitoring committee will be used for this trial. UC is consistent with the existing standard of care at the SingHealth Polyclinics. Additional elements, such as self-paced physical activity and financial incentives, do not involve more than minimal risk to the participants. This trial is subject to study review visits and/or audits by the SingHealth Research Quality Assurance unit which is responsible for ensuring that all investigator-initiated research processes are conducted suitably, adequately, effectively and efficiently across the SingHealth cluster. These study review visits/audits may be conducted routinely, triggered by CIRB or upon an investigator’s request.

### Statistical methods

#### Primary analysis

Change from baseline in HbA1c levels at month-6 will be linearly regressed on (1) binary variables indicating the intervention arms with UC as a reference category, (2) baseline HbA1c levels, (3) a binary variable indicating titration change and (4) other baseline characteristics (gender, age, language spoken, education, occupation, income, EQ-5D-5L, BIPQ, SMBG, BMQ and DSCA scores, and binary variables indicating comorbidities) in order to increase statistical efficiency. The analysis will be performed according to an intention-to-treat approach. All missing data will be imputed using Markov chain Monte Carlo multiple imputation. To test the robustness of the results, we will carry forward the last measured HbA1c level (baseline or month 3) for those participants who withdraw from the study as those intervention participants who do not achieve their goals might disproportionally withdraw from the study. The last measured HbA1c level will also be carried forward for those participants who are discontinued from the study after switching from oral to insulin therapy.

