### Objectives

#### Primary objective 1

To determine whether complementing UC with financial incentives for good treatment adherence is superior to UC alone in reducing HbA1c at 6 months.

#### Primary objective 2

To determine whether incentivising intermediate health outcomes (self-monitored blood glucose levels within acceptable range) is superior to incentivising intermediate processes (blood glucose testing, physical activity, and medication adherence) in reducing HbA1c at 6 months.

#### Secondary objective 1

To assess whether complementing UC with financial incentives for good treatment adherence is superior to UC alone in improving treatment adherence as measured by the proportion of glucose tests and medications taken as prescribed and average number of daily steps taken between baseline and 6 months.

#### Secondary objective 2

To assess whether incentivising health outcomes is superior to incentivising intermediate processes in improving treatment adherence as measured by the proportion of glucose tests and medications taken as prescribed and average number of daily steps between taken baseline and 6 months.

#### Secondary objective 3

To assess which intervention (i.e. incentivising health outcomes or processes) has the most favourable incremental cost-effectiveness ratio (ICER) for HbA1c reductions between baseline and 6 months compared to UC alone.

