### Sample size

A key parameter is the variability in post-intervention HbA1c levels. To assess this, we have used data from a pilot intervention aimed at improving diabetes outcomes through a comprehensive educational and management programme (that did not include financial incentives). Among 54 participants with suboptimally controlled diabetes, we found that the standard deviation in participant HbA1c levels was 1.29 at baseline and 1.99 after a 3-month intervention. Based on this data, we decided to use a standard deviation of 2 for the variability in post-intervention HbA1c levels to calculate the sample size for this trial.

We have first computed the size of the intervention arms that is required for testing whether there is a statistical difference between post-intervention HbA1c levels between the outcome and process incentive arms (primary objective 2). After applying a Bonferroni correction by dividing the test’s significance level by 2 (which is the number of primary hypotheses to test in this trial), we found that 76 participants per intervention arm are necessary to detect mean differences in HbA1c levels of 1% between these study arms (with significance level of 5/2 = 2.5% and 80% power). Given the resulting cumulated sample size for the intervention arms of 76 + 76 = 152, we then computed the size required for the UC arm to test the overall effect of financial incentives (primary objective 1) with the same effect size, significance level, and power. This computation yielded a sample size of 51 for the UC arm. After accounting for approximately 20% attrition in each study arm, we set the final sample size at 60 for the UC arm and 90 for each intervention arm, for a grand total of 240 participants.

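### The primary regression is not tied to the two primary hypotheses, and the fixed 2.5% split gives up power that Holm's procedure would recover

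*Protocol article*

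**What the plan says.** **Objectives.** Primary objective 1 asks whether "complementing UC with financial incentives for good treatment adherence is superior to UC alone in reducing HbA1c at 6 months". It concerns incentives as such, not one arm. Primary objective 2 asks whether outcome incentives beat process incentives.

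**Sample size.** The significance level is halved, two being the count "which is the number of primary hypotheses to test in this trial", and the calculation runs "with significance level of 5/2 = 2.5% and 80% power". The incentive arms are sized first, for "testing whether there is a statistical difference between post-intervention HbA1c levels between the outcome and process incentive arms"; this gives 76 per arm. The two arms are then added to 152, and the text continues "we then computed the size required for the UC arm to test the overall effect of financial incentives (primary objective 1"), which gives 51 in UC. The randomised numbers are 60, 90 and 90.

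**Primary analysis.** One linear regression contains "binary variables indicating the intervention arms with UC as a reference category", plus baseline HbA1c and other covariates. The section names no test, no contrast and no significance level.

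**Secondary analyses.** The cost-effectiveness analysis is conditional on the interventions, in the plural, improving HbA1c significantly. Each intervention is then compared with UC.

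**The concern.** The design defines two hypotheses and an error rate for each. The primary model, as parametrised, prints two coefficients, and neither is one of those hypotheses. The pooled effect and the outcome-minus-process difference both have to be built from the coefficients, and the article does not say that they will be.

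Two things are at stake. First, the decision rule for objective 1 could be the pooled contrast, either arm or both arms, and these differ in their chance of success. The trial is open-label, and HbA1c is examined after 80 and 160 completers, so the rule should be fixed beforehand. The plural condition for the cost-effectiveness analysis has the same ambiguity. Second, once the two tests are named, a fixed 2.5% for each is a valid but needlessly strict way to share 5%.

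**Working it through.** **Inputs** (Sample size section): difference 1 point; SD 2; 2.5% per hypothesis; 80% power; 76, 76 and 51 analysable; 60/90/90 randomised; about 20% attrition, which leaves 48/72/72. Sidedness is not stated. Two-sided is assumed because it reproduces the plan's figure (one-sided 2.5% would need 63 per arm).

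**1. The plan's own figures.** With z(0.9875) = 2.2414 and z(0.80) = 0.8416:
- Per incentive arm: 2 × 2² × (2.2414 + 0.8416)² / 1² = 76.04, against the stated 76.
- UC against 152: 2² × (3.0830)² = 38.02, then 1/(1/38.02 − 1/152) = 50.7, so 51 as stated.

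Both figures reproduce, so the pooled contrast is the design's own hypothesis for objective 1.

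**2. What the two-indicator model delivers at 51/76/76.** Power = Φ(1/SE − 2.2414).

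| Contrast | SE | Power at 2.5% |
|---|---|---|
| (process + outcome)/2 − UC | 2√(1/51 + 1/152) = 0.324 | 80.2% |
| outcome − process | 2√(2/76) = 0.324 | 80.0% |
| one arm − UC | 2√(1/51 + 1/76) = 0.362 | 69.9% |

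The first two standard errors, taken from the covariance matrix of the fitted coefficients, equal those of the direct comparisons. The choice of reference category therefore costs nothing.

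**3. Does the rule for objective 1 matter?** Take 48/72/72, each incentive arm 1 point better than UC, and 2.5% per test.
- One arm against UC: SE = 2√(1/48 + 1/72) = 0.373, power 67.1%. The two coefficients have correlation (1/48)/(1/48 + 1/72) = 0.6.
- Both arms significant (bivariate normal): 54%.
- Either arm significant: 2 × 67.1% − 53.8% = 80%.
- Pooled contrast: SE = 2√(1/48 + 1/144) = 0.333, power Φ(3 − 2.2414) = 77.6%.

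**4. Holm against the fixed split.** With equal incentive arms, the covariance of the two planned contrasts is half of Var(outcome mean) − Var(process mean), which is zero, so they are treated as independent. Holm tests the smaller p-value at 2.5% and, if that is significant, the other at 5%. The power for one contrast is

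p + (q − p) × p′,

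where p and q are its power at 2.5% and 5%, and p′ is the other contrast's power at 2.5%. Assume both contrasts truly equal 1 point:
- 48/72/72: p = p′ = 77.6%, q = Φ(3 − 1.960) = 85.1%. Result: 0.776 + 0.075 × 0.776 = 83.4%.
- 51/76/76: pooled 0.802 + (0.871 − 0.802) × 0.800 = 85.7%; outcome − process 0.800 + (0.869 − 0.800) × 0.802 = 85.5%. About 85.6% for each.
- If the other contrast is truly zero, p′ = 0.025 and the gain almost vanishes: 0.776 + 0.075 × 0.025 = 77.8% at 48/72/72.

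When both nulls hold, family-wise error is 1 − 0.975² = 4.9% under either procedure. When only one null holds, Holm's error for it is at most 5%.

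**The case against.** The Primary analysis section specifies a regression and not a set of tests. Coding UC as the reference is a convenience, and two indicators are what both objectives need, since a single pooled indicator could not answer objective 2. The hypotheses and the 2.5% level stand in the Objectives and Sample size sections, and an analyst can carry them over. Contrast formulas and repeated alpha levels are ordinary content of an analysis plan, which is not shown here. Bonferroni is valid and matches the sample size calculation.

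Most of this stands, and it rules out two stronger readings. A reader might infer that the plan tests the wrong, under-powered hypotheses, because a single arm against UC has only 69.9% power. The document never makes those coefficients the primary tests, and the planned contrasts keep their power. Part of the drop to 67.1% at 48/72/72 is attrition, which also lowers the planned contrasts to 77.6%. A reader might also infer inflated family-wise error, since three pairwise tests would give 12.2% at 5% each or 6.4% at 2.5% each. The document states two hypotheses, not three, and its two tests at 2.5% stay below 5%.

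The objection does not dispose of everything. The article fixes the hypotheses, the multiplicity rule and the reference category without connecting them, and its condition for the cost-effectiveness analysis can be read in three ways. Bonferroni's validity is no argument against a procedure that is never less powerful at the same family-wise error.

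**Conclusion.** The point holds as a missing link between model and hypotheses, together with a multiplicity rule that can be improved at no cost in patients. It is of moderate importance. It does not show a wrong analysis, a loss of power in the model or a breach of error control.

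Leaving the rule for objective 1 open moves its probability of success between 54% and 80% at 48/72/72 when both arms work by 1 point. Holm adds about 6 percentage points per contrast (77.6% to 83.4%, or about 80% to 85.6% at 51/76/76) when both contrasts are 1 point, which would mean process 0.5 and outcome 1.5 points better than UC. It adds next to nothing when one contrast is zero.

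These figures assume two-sided tests, normal approximations and the unadjusted SD of 2. Covariate adjustment would change all the powers by an amount that the document does not allow one to compute. A full analysis plan may already name the contrasts.

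**What to change.** Keep the regression and add to the Primary analysis section:

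- Primary test for objective 1: (process + outcome)/2 minus UC. Primary test for objective 2: outcome minus process. Both are two-sided and taken from the fitted model.
- Multiplicity: Holm over these two tests at an overall 5%, in place of the fixed 2.5% for each. The sample size calculation can stay as it is, since Holm is never less powerful than the split it assumes.
- The separate arm-versus-UC contrasts are secondary.
- In Secondary analyses, state which test result starts the cost-effectiveness analysis.

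The cost is wording only, with no extra patients or data. The one drawback is in the confidence intervals: those that match Holm are less simple than the 97.5% intervals that go with Bonferroni. If 97.5% intervals are reported anyway, one may include zero although Holm rejects at 5%, so the plan should say which intervals will be given. The change should be made before outcome data are compared by arm.

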#### Explanatory outcomes

*Mean change from baseline in glycated haemoglobin HbA1c at months 12 and 18*

*Proportion of participants whose oral medication was titrated up at months 6, 12 and 18*

*Proportion of participants who switched to insulin therapy at months 6, 12 and 18*

*Mean change from baseline in EQ-5D-5L* [21] *score at month 6* as a measure of functional health status. This scale has been validated in people with type-2 diabetes [22]. In Singapore, both the English and Mandarin versions have been validated in people with cancer [23]
*Mean change from baseline in Brief Illness Perception Questionnaire* [24] *(BIPQ) score at month 6*. This scale has been validated in English for multiple health conditions including diabetes [25]. The Mandarin version has been validated in Taiwan in people with coronary heart disease [26]
*Mean change from baseline in Self-Monitoring of Blood Glucose* [27] *(SMBG) score at month 6*. This scale has been validated in English in people with type-2 diabetes but has yet to be validated in Mandarin and in Singapore
*Mean change from baseline in general and specific scores of the* Beliefs about Medication Questionnaire [28] *(BMQ) at month 6*. The English version of the scale has been validated for several chronic diseases including diabetes [29] while the Mandarin version has been validated in other settings such as after mechanical heart-valve replacement [30] and depression [31]. Validity in Singapore has not been established for this scale
*Mean change from baseline in the exercise subscale of the Diabetes Self-Care Activities* [32] *(DSCA) at month 6.* The English version of the scale has been pretested for acceptability and comprehensibility in a study involving people with type-2 diabetes [32] but has neither been pretested in Mandarin nor in Singapore

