### Randomisation

Prior to the start of recruitment, randomisation numbers will be generated by the principal investigator of the study and the project coordinator using Stata 13.2 to create an assignment schedule for block-randomisation to allocate eligible participants into one of the three study arms in a ratio of 2:3:3. Whether participants are current glucometer users or not (current vs. new glucometer users) will be used as the blocking factor, and the block size will not be communicated to study site in order to minimise the predictability of the random sequence. The project coordinator and the principal investigator of the study will then store the assignment schedule (including generation information) on a secure server at Duke-NUS. For allocation concealment, the project coordinator and a witness external to the study will enclose the assignments in sequentially numbered, opaque, sealed, randomisation envelopes and the project coordinator will hand these to the CRC along with other relevant study materials. Note that the behavioural nature of the intervention precludes masking the arm allocation to both the study team and participants. The allocation will be revealed to both the CRC and participant upon enrolment. However, the study arm assignment will be not be revealed to the laboratory staff assessing the primary outcome (HbA1c test).

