Each pedometer will be linked to an anonymous online Fitbit™ account that will be created for the study. The trial application will automatically synchronise with the Fitbit™ accounts and automatically update physical activity data for adherence and incentives calculations. This data will be checked regularly by the project coordinator to verify that the participants are synchronising their pedometer with their Fitbit™ account and that this data gets transmitted to the trial application. This is important because the pedometers can store up to 30 days of data. Participants who do not synchronise for 21 days will receive an automatic text message to remind them to synchronise. Participants who do not have access to a smartphone or personal computer will need to come to the polyclinic once a month where the CRC will synchronise their pedometers for them.

Paper-based survey questionnaires will be administered at baseline and month 6 by the CRC. Both questionnaires include the European Quality of Life-5 Dimensions-5 Levels,(EQ-5D-5L), BIPQ and BMQ survey instruments. The baseline survey also includes patient socioeconomic characteristics while the month-6 questionnaire contains questions on compliance with the medication tracker and medication-purchasing habits during the intervention period.

In addition, the CRC will complete participant checklists at baseline, months 3, 6 and 18. The Baseline checklist will include the participant’s current HbA1c reading and the date of the blood test. This information will be obtained from the SingHealth computerised patient database at Geylang Polyclinic. The randomisation code and study arm, the participants’ diabetes medication regimen, and whether the participants are new or current glucometer users will also be recorded on the checklist. The CRC will also confirm the participants have understood which study arm they have been randomised to, record the response on the checklist and explain again if necessary.

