At months 3 and 6, the CRC will again check that the participant understands the goals and rewards of the study arm they have been randomised to, record the response on the corresponding checklist and re-explain if necessary. Details on fasting which could affect medication dosages and times; overseas trips which involve time zone changes that will possibly impact the study devices; and hospitalisations will also be recorded at months 3 and 6. Further, the participants’ adherence and payments made will be recorded along with the time spent by the CRC on adherence calculation and corresponding incentive payments. Last, the CRC will record any changes to the participants’ diabetes medication regimen based on their medical records.

At month 18, the CRC will complete a checklist solely from the patient’s medical records. This checklist will include recording HbA1c results and any changes in medication regimen since the patient completed the intervention.

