### Explanatory analyses

The same model as for the primary analysis will be conducted with changes from baseline in HbA1c levels at months 12 and 18. Logistic regressions of binary variables indicating whether the participants have had a titration change of their oral medicine, and whether they have switched to insulin therapy at months 6, 12 and 18 will be estimated. Linear regressions of the changes from baseline in EQ-5D-5L, BIPQ, SMBG, BMQ and DSCA scores at month 6 will also be estimated. For all models, the covariates will be binary variables indicating the intervention arms and the same other baseline characteristics as for the primary analysis. Next, the models used in the primary and secondary analyses will be extended by adding interaction terms between potential intervention moderators (gender, age, language spoken, education, occupation, income, EQ-5D-5L, BIPQ, SMBG, BMQ and DSCA scores, and binary variables indicating comorbidities) and the binary variables indicating study arms. In particular, this analysis will be used to determine the benefit incidence of the intervention according to socioeconomic factors.

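### The primary HbA1c model adjusts for titration change, a post-randomisation variable and trial outcome, so its arm coefficients need not estimate the total effect of assignment

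*Protocol article*

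**What the plan says.** All references are to the protocol article.

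- **Statistical methods, Primary analysis.** Month-6 change in HbA1c is regressed on arm (usual care, UC, as reference), baseline HbA1c, "3) a binary variable indicating titration change and (4) other baseline characteristics". The reason given for the covariates is statistical efficiency. The section adds: "The analysis will be performed according to an intention-to-treat approach". Its only robustness check concerns carrying HbA1c values forward; no version of the model without the titration term is planned.
- **Outcome measures, Explanatory outcomes.** One listed outcome is: "Proportion of participants whose oral medication was titrated up at months 6, 12 and 18".
- **Explanatory analyses.** Titration appears as a dependent variable, with arm among the covariates: "Logistic regressions of binary variables indicating whether the participants have had a titration change of their oral medicine".
- **Data collection.** At baseline the checklist takes the current regimen: "the participants’ diabetes medication regimen, and whether the participants are new or current glucometer users will also be recorded on the checklist". At months 3 and 6, "the CRC will record any changes to the participants’ diabetes medication regimen based on their medical records". No titration change before randomisation is defined anywhere.
- **Randomisation.** The trial is open label: "the behavioural nature of the intervention precludes masking the arm allocation to both the study team and participants".

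**The concern.** A covariate improves precision without altering the target of estimation only if treatment cannot affect it. Titration change occurs after randomisation, and the trial plans to test whether arm affects it. Holding it fixed can do two things:

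- remove whatever part of the arm effect on HbA1c acts through changes in medication;
- open a non-causal path, because patients with a poorer underlying course may be more likely to be titrated, so that patients with equal titration status are no longer comparable across arms.

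Both primary objectives ask whether assignment reduces HbA1c at 6 months. What is at stake is whether the reported coefficients answer that. The cost-effectiveness analysis inherits the problem, since it is triggered by a significant HbA1c improvement and takes the primary outcome as its measure of effect.

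**Working it through.** **1. Is the covariate measured after randomisation?** Baseline supplies a regimen and months 3 and 6 supply changes to it. Titration is an outcome at months 6, 12 and 18. The word *other* before the baseline characteristics might suggest a baseline item, but the article defines none.

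**2. Can arm affect it?** Allocation is unmasked. Under Arm 1: Usual care (UC), follow-up is every 2 to 4 months according to glycaemic control, and HbA1c can be tested before the physician visit. An arm that changes glycaemic control could therefore change titration. This is an inference; the article does not say what prompts titration of oral medication.

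**3. The plan's own figures (Sample size).** Inputs: SD 2, difference 1.0, alpha 0.025 (two-sided fits; one-sided would give 63), power 80%.
- Objective 2: n per arm = 2 × (2.241 + 0.842)² × 2² / 1² = 76.04, against 76 stated.
- Objective 1: against 152 pooled, the smallest UC arm with at least 80% power is 51 (power 0.802), as stated.
- Standard errors: 2 × √(2/76) = 0.324 and 2 × √(1/152 + 1/51) = 0.324.

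The calculation uses an unadjusted SD, so deleting the term changes neither figure.

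**4. How far the arm coefficient moves.** For least squares, exactly:

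arm contrast without the term − arm contrast with the term = (titration coefficient) × (covariate-adjusted difference in titration for that contrast).

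With an assumed coefficient of 0.5 to 1.0 HbA1c points and an assumed difference of 5 to 20 percentage points, the shift runs from 0.5 × 0.05 = 0.025 to 1.0 × 0.20 = 0.20. If titration does not differ, it is 0. For objective 2 the relevant difference is that between the two incentive arms.

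**5. Illustrative simulation** (pooled incentive against UC, 3:1; 1,000,000 participants per scenario; all inputs assumed except the baseline SD of 1.29 from Sample size). With baseline B, latent prognosis U (SD 1) and arm A:
- interim HbA1c = 0.6B + U + 0.8δA + error (SD 0.5);
- titration T is logistic with intercept −1 and slope s on interim HbA1c, plus a direct arm term d;
- month-6 HbA1c = 0.6B + U + δA + gT + error (SD 1).

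Change was regressed on A and B, without and then with T.

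| δ, g, s, d | Titrated, UC / incentive | Without T | With T | Shift |
|---|---|---|---|---|
| 0, 0, 1.0, 0 | 32% / 32% | 0.002 | 0.002 | 0.000 |
| −0.5, 0, 1.0, 0 | 32% / 26% | −0.495 | −0.442 | +0.052 |
| −1.0, 0, 1.0, 0 | 32% / 20% | −1.004 | −0.907 | +0.097 |
| −1.0, −1.0, 0.5, 0 | 29% / 22% | −0.928 | −0.965 | −0.037 |
| 0, 0, 0.5, +0.7 | 29% / 43% | 0.003 | −0.065 | −0.068 |

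The shift goes in either direction. The last row produces an apparent effect where none exists, but only by assuming that arm acts directly on prescribing, which nothing in the article supports. Across all scenarios run, shifts were between 0 and about 0.10 in size.

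**6. Scale.** A shift of 0.10 is 0.10 / 0.324 = 0.3 planned standard errors. Holding the standard error at 0.324, a true 1.0 estimated as 0.90 has power Φ(0.90/0.324 − 2.241) = Φ(0.53), about 70%; estimated as 0.80, Φ(0.23), about 59%. The Background cites average HbA1c reductions of 0.20 to 0.57 points for other interventions, which the Discussion names as comparators.

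**The case against.** The strongest defence is that the bias may be nil. If titration runs equally in all arms, the coefficients with and without the term agree, and the article gives no rates to suggest otherwise. That stands as a limit on what can be claimed about size. It does not justify the term, because the primary analysis should not depend on a condition that the trial itself plans to test.

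It might also be said that the term isolates a behavioural effect net of medication. That would be a different estimand with its own no-confounding assumptions. The article does not declare it; the reason it gives is efficiency.

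Several stronger readings are tempting but not supported:

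- *That the model contradicts the intention-to-treat statement.* Everyone can still be analysed as randomised with a poorly chosen covariate. What may be lost is the total effect of assignment.
- *That physicians titrate in response to HbA1c and adherence, knowing the arm.* No section states the trigger, says that the coordinator's adherence data reach the prescriber, or says that treating physicians are told the allocation.
- *That both objectives are shown to be biased.* The simulations compare incentive with UC only. Objective 2 is affected only if titration differs between the process and outcome arms.
- *That the month-12 and month-18 models carry the term.* Explanatory analyses first refers to the primary model, then describes the covariates of all its models as arm and the other baseline characteristics. It can be read either way.
- *That reductions in medication will be counted as increases.* The phrase "whether the participants have had a titration change of their oral medicine" may be shorthand for the up-titration outcome. This is a wording mismatch in an explanatory analysis.

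**Conclusion.** The point holds for the primary model as written. It includes a post-randomisation variable that is also a trial outcome, and no primary model without it is planned. If arm affects titration, the arm coefficients do not estimate the effect the objectives name, and a larger sample would not correct this.

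The direction is unknown. The range of about 0 to 0.2 HbA1c points rests wholly on assumed titration coefficients and arm differences. That is modest beside the planned 1.0, but not beside the effects the article intends to compare with. The case for change rests on the choice of covariate and the negligible cost of correcting it, not on a demonstrated bias of any given size.

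**What to change.** 1. Delete item (3) from the primary model and adjust only for variables fixed before randomisation. If a titration history before enrolment was meant, define it as such.
2. Keep titration as an explanatory outcome. Label any titration-adjusted HbA1c model exploratory.
3. State that the month-12 and month-18 models also omit the term.
4. Minor: use one definition of titration in Explanatory outcomes and Explanatory analyses.

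This takes a few sentences in the protocol or analysis plan, with no new data and no change to the sample size. The downside is the loss of any residual variance that titration explained. Trial status reports recruitment still under way (140 of 240 enrolled), so the change could be made before the final analysis.
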